## Abstract

Meal replacement (MR) is widely used in weight and diabetes management programs due to its ease of compliance and handling. However, little is known about its impact on outcomes other than glycaemic control and weight loss. Furthermore, not many studies evaluate its cost-effectiveness and sustainability. This study aimed to evaluate the efficacy of a diabetes-specific MR for the weight reduction and glycaemic controls of overweight and obese T2DM patients, as compared to routine dietary consultation. Other health outcomes, the cost effectiveness, and the sustainability of the MR will also be evaluated. Materials and Methods: This randomised controlled clinical trial will involve 156 participants who have been randomised equally into the intervention and control groups. As a baseline, both groups will receive diet consultation. Additionally, the intervention group will receive an MR to replace one meal for 5 days a week. The duration of intervention will be 12 weeks, with 36 weeks of follow-up to monitor the sustainability of the MR. The primary endpoints are weight and Hemoglobin A1c (HbA1c) reduction, while the secondary endpoints are anthropometry, biochemical measurements, satiety, hormone changes, quality of life, and cost-effectiveness. The impact of the COVID-19 pandemic on study design is also discussed in this paper. This study has obtained human ethics approval from RECUKM (JEP-2019-566) and is registered at the Thai Clinical Trials Registry (TCTR ID: TCTR20210921004).

## 1. Introduction

Obesity is one of the biggest ongoing health concerns, with 1.9 billion adults worldwide who are either overweight or obese [1]. Among Southeast Asia countries, Malaysia has the highest prevalence of obesity among adults [2]. Based on the National Health and Morbidity Survey 2019 findings, the prevalence of an overweight or obese status among Malaysian adults has reached a concerning level of 50.1% [3].

Obesity is closely linked to Type-2 Diabetes Mellitus (T2DM). In fact, obesity itself causes insulin resistance, specifically in visceral obesity. In 38 out of 44 studies pooled in a systematic review on the prevalence of obesity among T2DM patients, over 30% of participants are reported as obese [4].

As reported by the International Diabetes Foundation (2017), approximately 451 million people worldwide are affected by T2DM, and the number is expected to increase to 693 million by the year 2045 [5,6]. The latest National Health and Morbidity survey has reported that the prevalence of diabetes in Malaysia is 18.3%, with an increase of 4.9% since 2015 [3].

Efforts for effective lifestyle intervention and management of T2DM tailored for overweight and obese patients are essential for weight reduction and the improvement of glycaemic control among T2DM patients. Meal replacement is a term which refers to pre-packaged or commercially available food products or drinks used to replace one or more meals [7]. A systematic review that involves 23 studies and 7884 adults showed that subjects who received meal replacement lost more weight, compared to those who received other diet plans or only consultation [8]. Furthermore, incorporating meal replacement as part of a comprehensive lifestyle intervention has also been found to be effective in reducing HbA1C and facilitating the initial weight loss of 5145 overweight or obese T2DM participants, as reported in one of the largest diabetes weight management studies, the Look AHEAD study [9,10,11].

However, there are still limitations faced by some of the existing meal replacement formulations, such as the risks of side effects. There is a cohort study on 8361 participants that shows that a very low-calorie diet (VLCD) increases the risks of symptomatic gallstones that require a cholecystectomy [12]. Certain liquid meal replacements do not contain enough fibre, which may lead to undesired effects in the bowel system if consumed daily. T2DM patients, who require daily adequate nutrient intake, also often suffer from nutrient deficiencies [13].

While meal replacement can lead to greater initial weight loss and glucose control, there is still a lack of evidence on the long-term feasibility of the sustained use of meal replacements [14]. Once the meal replacement intervention is reduced or discontinued, its benefit of glycemic control and weight reduction may not be sustained [15]. The cost of meal replacement might also be a barrier for long-term consumption, as it can be an economic burden for patients. In most clinical trials, meal replacement is often subsidized, or provided for free, to subjects during the initial intervention. Upon completing the initial intervention, participants are often unwilling to pay for long term therapy [16]. Once the subsidised meal replacement is reduced or completely discontinued, the benefits may be reversed, as shown in a study by Keogh and Clifton [15].

Hence, in this study we are going to evaluate the effectiveness and sustainability of a nutritionally balanced diabetes-specific meal replacement in weight reduction and glycaemic parameters controlled for overweight and obese patients with T2DM, as compared to normal dietary consultation. We are also going to assess the effect of meal replacement on satiety level and hormonal changes, as well as the cost-effectiveness of meal replacement when compared to standard care. This will be the first randomised controlled trial to utilise the diabetes-specific meal replacement *Metabolic Sauver* among T2DM patients.

The results from this study can help in providing input towards the future development of lifestyle modification modules that incorporate short-term meal replacement therapy to be utilised in clinical settings. This can help in our fight against the disease and ease the burden of T2DM on the nation’s healthcare and economy.

In this article, we also discussed the impact of the COVID-19 pandemic on the recruitment and enrollment process of this ongoing clinical trial. The COVID-19 pandemic has affected over 172 million people worldwide, with 616,845 people testing positive for COVID-19 in Malaysia as of June 2021 [17]. It remains a crisis in the country as authorities have redirected most of their resources towards handling COVID-19 patients. The measures taken by the authorities can be impactful towards clinical trial research, which is deemed as a desirable but not an essential activity. The pandemic can affect clinical trials in various ways, such as the completion of trial assessments, patient visits to clinical settings, and stock shortages for investigational medicinal products. It is important to assess and understand the impact of the COVID-19 pandemic for effective countermeasures to ensure the success of our clinical trial.

### 1.1. Research Objective

Our research objective is to determine the effect and sustainability of diabetes-specific meal replacement on weight reduction (weight, BMI, body composition) and glycemic control (HbA1c, fasting blood glucose) among obese or overweight T2DM participants. We are also going to assess the effect of meal replacement on satiety level, hormonal changes (adiponectin, leptin, ghrelin, obestatin, peptide YY) and the quality of life among the participants. Cost-effectiveness will also be evaluated, as compared to standard care.

#### 1.1.1. Primary Endpoint

Changes in HbA1c and bodyweight from the beginning of treatment to week 12 after initiation of treatment

#### 1.1.2. Secondary Endpoint

BMIBody CompositionWaist and hip circumferenceFasting blood glucoseInsulin resistance index (HOMA-IR)Lipid ProfileSatiety levelHormonal ChangesQuality of lifeCost-effectiveness

## 2. Methodology

### 2.1. Study Design

The study design is a two-armed randomised controlled clinical trial. Participants will be recruited into the study based on the inclusion and exclusion criteria (Table 1). Five thousand one hundred and eighty-five patients are screened through digital medical records in the database for their eligibility to be potentially recruited into the study.

Eligible and consenting participants will be randomised into two groups: (a) Meal replacement group (MR) and (b) Control group. The MR group will be receiving a meal replacement product and dietary consultation, while the control group will be receiving dietary consultation only. Outcome measurements will be assessed at the baseline, 6th week and after the completion of the 12-week intervention. Sociodemographic data, dietary information, and the quality of life of participants will also be recorded via questionnaires. Participants will also be monitored for 36 weeks after the completion of the meal replacement without any additional intervention. Another follow up will be done in week 48 and the same parameters will be measured. Hence, the total duration of the study is 48 weeks. A brief research flow chart is shown below in Figure 1.

### 2.2. Sample Size

Sample size is calculated using G *Power 3.1 software. The protocol for calculation is as shown below in Table 2. We employed an effect size of 0.2055067, which is obtained from the mean difference value of the HbA1c (%) result in a study by Keogh and Clifton [18]. Based on the calculation, a total of 120 participants is needed for the study. In order to account for up to a 30% dropout, a total of 156 participants will be recruited for this study.

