## Figures and Tables

**Figure 1 ijerph-19-04188-f001:**
[figure not shown]
Research Flow Chart.

**Table 1 ijerph-19-04188-t001:** Inclusion and Exclusion Criteria.

Inclusion Criteria	Exclusion Criteria
Aged 20–65 years old	On insulin treatment
Diagnosed with T2DM for at least 6 months with baseline HbA1c levels between 7.5% and 12% for the past 3 months	With chronic kidney disease or on continuous ambulatory peritoneal dialysis or hemodialysis (GFR < 30 mL/min/1.73 m^2^)
Overweight or obese with BMI ≥ 25 kg/m^2^	With hepatic diseases (ALT > 120 IU/L)
On stable doses of any oral hypoglycaemic agents for the past 3 months	With history of chronic alcohol abuse
	Pregnant and lactating women
	Currently consuming any weight reduction products or any slimming prescriptions
	Currently involving in weight loss programs
	Record of COVID-19 diagnosis

**Table 2 ijerph-19-04188-t002:** Protocol for calculation in G*Power.

Sample Size Calculation	
F tests—ANOVA: Repeated measures, between factors	
Analysis: A priori: Compute required sample size	

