**Input**	
Effect size f	= 0.2055067
α err prob	= 0.05
Power (1-β err prob)	= 0.80
Number of groups	= 2
Number of measurements	= 4
Corr among rep measures	= 0.5

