**Output**	
Noncentrality parameter λ	= 8.1087367
Critical F	= 3.9214782
Numerator df	= 1.0000000
Denominator df	= 118
Total sample size	= 120
Actual power	= 0.8063091

**Table 3 ijerph-19-04188-t003:** Data collection Table.

Data Collected/Session	Week 0	Week 6	Week 12	Week 24	Week 36	Week 48
Socio-demography information	/					
Global Physical Activity Questionnaire	/		/	/	/	/
Dietary Assessment						
3-day dietary recall	/	/	/	/	/	/
Food Frequency Questionnaire	/	/	/	/	/	/
Anthropometry Measurements						
Height	/	/	/	/	/	/
Weight	/	/	/	/	/	/
Neck circumference	/	/	/	/	/	/
Waist circumference	/	/	/	/	/	/
Hip circumference	/	/	/	/	/	/
Body composition (muscle mass, fat mass, fat percentage)	/	/	/	/	/	/
Metabolic Profiles						
HbA1c	/		/			/
Fasting Blood Glucose	/		/			/
Insulin Resistance Index (HOMA-IR)	/		/			/
Lipid profile	/		/			/
Renal Profile	/		/			/
Liver Profile	/		/			/
Hormone related to Glycemic Control						
Adiponectin, Leptin	/		/			/
Satiety Measurements						
VAS	/	/	/	/	/	/
Ghrelin, obestatin, peptide YY	/		/		/	/
Quality of life						
ADDQOL-19	/		/	/	/	/
DTSQ	/		/	/	/	/
DDS	/		/	/	/	/
Cost-effectiveness						
EQ-5D-5L	/		/	/	/	/

**Table 4 ijerph-19-04188-t004:** Sociodemographic of participants identified (n = 136).

Parameters	Numbers/Mean
Gender	
Male	81 (59.5%)
Female	55 (40.5%)
Age	54.9 ± 9.3
Race	
Malay	87 (63.97%)
Chinese	25 (18.38%)
Indian	21 (15.44%)
Others	3 (0.02%)
Duration of diagnosis for T2DM (Years)	6.4 ± 4.3
HbA1c Levels (%)	8.5 ± 1.0
Fasting Plasma Glucose (mmol/L)	8.6 ± 2.5

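### The recruitment target of 156 retains the required 120 participants only up to about 23% dropout, not the stated 30%, because 120 was multiplied by 1.3 instead of divided by 0.7

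*Protocol article*

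**What the plan says.** Section 2.2 (Sample Size) reports a G*Power calculation: "We employed an effect size of 0.2055067", taken from an HbA1c result in an earlier study, and then "Based on the calculation, a total of 120 participants is needed for the study". The next sentence makes the dropout allowance: "In order to account for up to a 30% dropout, a total of 156 participants will be recruited for this study". The Abstract repeats 156, split equally between the arms.

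Table 2 gives the details. The procedure is "F tests—ANOVA: Repeated measures, between factors", with "α err prob = 0.05", "Power (1-β err prob) = 0.80" and "Number of groups = 2", four measurements and a correlation of 0.5 among them. Its output line "Total sample size" is 120, with an actual power of 0.8063091. Table 2 has no dropout input, so 120 is the number the calculation needs after losses. The article nowhere defines the 30% as a share of those who complete, and nowhere gives a different number for it.

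**The concern.** A dropout rate is ordinarily the share of recruited participants who are lost. To keep n participants after losing a fraction d, one recruits n/(1 − d). Multiplying by (1 + d) gives a smaller number, and the gap widens as d grows. At 30% it is no longer a rounding matter.

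At stake is whether the trial has the protection that Section 2.2 claims. If dropout reaches the stated ceiling, the trial falls below both its own required size and its own power target. The figure also has a practical role, because Section 2.3 says recruitment continues until the required number is reached.

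**Working it through.** **Inputs.** From Section 2.2: N = 120 needed, 156 recruited, dropout up to 30%. From Table 2: f = 0.2055067, α = 0.05, target power 0.80, 2 groups, m = 4 measurements, correlation ρ = 0.5. From Section 2.5: 1:1 allocation.

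**Step 1: reproduce Table 2.** For the between-groups test in a repeated-measures ANOVA:

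- λ = N × f² × m / (1 + (m − 1)ρ)
- f² = 0.2055067² = 0.042233, and m / (1 + (m − 1)ρ) = 4 / 2.5 = 1.6
- At N = 120: λ = 120 × 0.042233 × 1.6 = 8.1087
- With 1 and 118 degrees of freedom, the critical F is 3.9215 and the power is 0.8063

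All of these match Table 2, so the 120 reproduces from its stated inputs.

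**Step 2: reproduce 156.**

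- 120 × (1 + 0.30) = 156.0, exactly the stated figure
- 120 / (1 − 0.30) = 171.4, rounded up to 172 (86 per arm)

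The stated figure therefore comes from multiplication and is 172 − 156 = 16 below the number that matches the claim.

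**Step 3: what 156 delivers.**

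- At 30% dropout: 156 × 0.70 = 109.2, so about 109 remain, which is 120 − 109 = 11 short
- Largest dropout that leaves 120: 1 − 120/156 = 36/156 = 23.1%

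**Step 4: power on the same method.**

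| N analysed | λ | Power |
|---|---|---|
| 120 | 8.109 | 0.806 |
| 119 | 8.041 | 0.803 |
| 118 | 7.974 | 0.7996 |
| 109 | 7.365 | 0.767 |

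At N = 109 the shortfall is 0.806 − 0.767 = 0.039 against the stated power and 0.80 − 0.767 = 0.033 against the target. The smallest N that reaches 0.80 is 119, so 156 holds the power target up to 1 − 119/156 = 23.7% dropout. Table 2 thus has almost no slack to absorb the difference.

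**The case against.** The arithmetic is hard to dispute, but four points bear on how much it matters.

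- **The ceiling may not be reached.** The text says up to 30%. If dropout stays at or below about 23%, the trial keeps its 120. This stands, and it limits the consequence. It does not make the sentence correct, since 30% is the planning figure the authors chose.
- **The 30% has no time frame.** The primary endpoint is at week 12 (Section 1.1.1), while the study runs to week 48 (Section 2.1). If 30% is the loss over the whole study, anyone who leaves after week 12 has already contributed both primary outcomes, and more than 109 would be available at week 12. This stands. The figure of 109 assumes that the whole 30% is lost before the primary analysis.
- **The main analysis is not restricted to completers.** Section 2.9 plans an intention-to-treat analysis with missing values handled under missing-at-random, and Table 3 has weight measured at week 6. Some early leavers will therefore inform the weight comparison. For HbA1c, Table 3 has nothing between weeks 0 and 12. Predicting missing values does not recover the information lost with participants who leave, so this softens the effect for weight without repairing the inflation step.
- **The remedy can leave the design untouched.** This is also true, and it argues against treating the point as critical.

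A reader might infer something stronger: that the dropout error leaves the trial seriously underpowered, for example by recomputing power for a single comparison of week-12 change or a baseline-adjusted week-12 analysis. The documents do not support blaming that on the dropout step. If f is read as a standardised difference of 2 × 0.2055 = 0.411 at one time point, with correlation 0.5, those tests already give only about 0.61 and 0.73 at the full 120. Falling to 109 costs each of them about 4 points, much as it does on the stated method. The rest of the gap comes from replacing the Table 2 test with another one, which is a separate question.

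**Conclusion.** The concern holds for the dropout step. Section 2.2 claims cover for 30% dropout, and 156 gives cover for about 23%. At 30% about 109 remain and power on the Table 2 method is about 0.767, below the 0.80 target and about 4 points below the stated 0.806.

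This rests on reading dropout as a share of those recruited, on all of the 30% being lost before the primary analysis, on leavers contributing nothing, and on Table 2's own inputs taken as given. The first is the ordinary meaning, and nothing in the article defines it otherwise. The second and third make 0.767 the unfavourable end.

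The size is modest. There is no bias and no effect on the type I error. The statement is wrong as written and easy to correct, so it should be fixed, but it does not threaten the validity of the trial.

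**What to change.** Restate the last sentence of Section 2.2. It should say that recruiting 156 retains 120 participants at up to about 23% dropout, and that at 30% dropout about 109 would remain, with power of about 77% on the stated method. It would help to add whether the dropout figure refers to week 12 or to week 48.

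This costs one sentence and a slightly less favourable stated figure. Sample size, design and analysis stay as they are.

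If the 30% claim is to be kept instead, the matching target is 172 (86 per arm), 16 more participants, and the Abstract's 156 would have to change with it. Section 3 reports 136 participants identified and the intervention not yet begun, so at the time of writing either route was still open.

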### 2.3. Recruitment

Participants will be recruited from the outpatient clinic of Hospital Canselor Tuanku Muhriz’s Primer Clinic of the National University of Malaysia via purposive sampling. Potential participants will be identified from the computerized medical record database according to the inclusion and exclusion criteria stated in Table 1. Invitations will be sent to potential participants via phone call and email. Interested participants will be invited to attend a screening. Prior to the screening process, detailed information about this study will be explained, and written consent (Online Supplementary File 1) will be obtained. Recruitment will be an ongoing process throughout the study until the required number of participants is achieved. This study will be carried out in accordance with the Helsinki Declaration of 1975, as revised in 1989, which states that no vulnerable participants should be recruited. The study is currently in the recruitment phase. The screening process started in September 2020. The recruitment process has been halted a few times due to the COVID-19 pandemic in Malaysia.

### 2.4. Baseline Screening and Assessment

Subsequent to the recruitment, participants who have provided consent will be directed to the clinic for baseline assessment. Anthropometry and body composition measurements will be recorded. A research dietician will assess the dietary intake of the participants with a 3-day dietary recall and food frequency questionnaire on added sugar intake. Eighteen millilitres of blood will be collected by a qualified phlebotomist to measure HbA1c, fasting plasma glucose, fasting insulin, lipid, renal, liver profiles, and hormonal changes. Instruments to measure satiety, quality of life, and cost effectiveness will also be administered. A detailed list of baseline measurements is shown in Table 3, and the methods used for measurements are shown in the ‘data collection’ section.

### 2.5. Randomisation

Following the baseline measurement, participants will be randomised into the MR group and control group at a 1:1 ratio. A third-party statistician will carry out the randomisation using the Winpepi computer program with minimisation method [19]. Gender (men, women), HbA1c (≤8.5% or >8.5%), and BMI (≤25 or >25) at the time of baseline measurement will be balanced in each group. Treatment allocation will not be blinded to both researchers and participants due to the nature of the intervention. The participants will be informed about which group they should accordingly be in before the intervention process starts.

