## 3. Impact of COVID 19 on Data Collection

### Preliminary Result

The study is currently in the recruitment and initial intervention phase. A total of 5185 patients were screened between September 2020 to May 2021 from digital medical records. A total of 136 participants were identified to be recruited. The intervention process has not yet been started. The overall distribution of participants identified by gender, age, and race is shown in Table 4 below. The overall mean age (±SD) of the participants is 54.9 ± 9.3 years. Among them, there are 81 males and 55 females with predominantly 63.97% Malay, 18.38% Chinese, 15.44% Indian, and 0.02% others. Overall, HbA1c levels of the participants averaged 8.5 ± 1.0%, while fasting plasma glucose levels averaged 8.6 ± 2.5 mmol/L.

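### The BMI minimisation factor is cut at 25 although entry already requires BMI of at least 25, so the minimisation does almost nothing to balance BMI

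*Protocol article*

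**What the plan says.** Section 2.5 (Randomisation) sets out minimisation, run by a third-party statistician in WinPepi, under which "participants will be randomised into the MR group and control group at a 1:1 ratio". Three factors are named: gender, HbA1c cut at 8.5%, and BMI cut at 25. Of these the section says: "and BMI (≤25 or >25) at the time of baseline measurement will be balanced in each group".

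Table 1 (Inclusion and Exclusion Criteria) requires: "Overweight or obese with BMI ≥ 25 kg/m^2".

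Both statements are current text. No other BMI cut for allocation appears in the article.

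The primary endpoint (section 1.1.1) is: "Changes in HbA1c and bodyweight from the beginning of treatment to week 12 after initiation of treatment". On size, section 2.2 says: "In order to account for up to a 30% dropout, a total of 156 participants will be recruited for this study".

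**The concern.** A minimisation factor works only if participants are spread over its levels. Here the cut sits on the entry boundary, so one level is all but empty. The HbA1c factor shows the contrast. Its cut of 8.5% equals the mean of the patients already identified (8.5 ± 1.0% in Table 4), so it divides the sample.

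Body weight is one of the two primary endpoints and BMI is computed from weight. By naming BMI as a factor, the protocol itself treats it as worth controlling. As written, the rule cannot deliver that control, and a reader of the final report would be told that BMI was balanced by design when it was left to chance.

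**Working it through.** **Inputs from the article.** BMI levels ≤25 and >25 at baseline (section 2.5). Entry at BMI ≥25 (Table 1). Planned total 156, allocated 1:1 (sections 2.2 and 2.5), hence 156/2 = 78 per arm. 59.5% men and HbA1c 8.5 ± 1.0% (Table 4). The article reports no BMI distribution, so every BMI mean, SD or obesity share below is an assumption.

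**Plan's own figure.** The sample size in Table 2 reproduces: λ = 0.2055067² × 120 × 4/(1 + 3 × 0.5) = 8.1087, critical F 3.9215, power 0.8063. This point does not depend on it.

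**Step 1: overlap of levels and entry range.** The set BMI ≥25 meets the set BMI ≤25 only at 25. All other eligible values belong to the level >25.

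**Step 2: how many participants that is.** Take BMI as normal and truncated at entry. If BMI is recorded to 0.1, the share at exactly 25 is P(24.95 ≤ X < 25.05)/P(X ≥ 24.95).

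| Assumed mean, SD | Share, recorded to 0.1 | Expected of 156 | Share, recorded to 0.01 | Expected of 156 |
|---|---|---|---|---|
| 28, 4 | 0.97% | 1.5 | 0.10% | 0.15 |
| 30, 5 | 0.57% | 0.9 | 0.06% | 0.09 |
| 32, 5 | 0.33% | 0.5 | 0.03% | 0.05 |

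At most one or two participants would sit in the lower level.

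**Step 3: chance imbalance left over.** Let p be the share with BMI ≥30. The SD of the between-arm difference in that share is sqrt(p(1 − p)(1/78 + 1/78)).

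- p = 0.5: sqrt(0.25 × 2/78) = 0.080; 1.96 × 0.080 gives about 16 percentage points (15.7).
- p = 0.3 or 0.7: sqrt(0.21 × 2/78) = 0.073, giving about 14 points.

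**Step 4: simulation.** 156 participants, 3,000 runs, deterministic minimisation, BMI assumed normal (mean 30, SD 5) and truncated at 25.

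| Rule | SD of difference in mean BMI | Chance of a difference above 1 kg/m² | 95th percentile of absolute difference in share ≥30 |
|---|---|---|---|
| No BMI factor | 0.62 | 10% | 15.4 points |
| Cut at 25 (as planned) | 0.64 | 12% | 15.4 points |
| Cut near 30 | 0.40 | 1% | 1.6 points |

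The first two rows can be checked by hand. The truncated variance is 25 × (1 − 0.2876 − 0.2876²) = 15.74, where 0.2876 = 0.24197/0.84134, so the SD is 3.97. The SD of the difference in means is then 3.97 × sqrt(2/78) = 0.64, and the chance of exceeding 1 kg/m² is about 11.5%. The share ≥30 is 0.5/0.84134 = 0.594, and 1.96 × sqrt(0.594 × 0.406 × 2/78) = 0.154. The planned cut therefore performs like having no BMI factor. A cut inside the eligible range restores most of the protection.

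**The case against.** The strongest reply is that little is at risk. An almost constant factor does not bias allocation or raise the type I error. BMI is still balanced in expectation, and HbA1c, the other primary endpoint and the basis of the sample size, has a factor that works. All of this stands, and it rules out the reading that the trial's comparison is compromised.

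A reader might also infer that BMI is the main baseline correlate of the weight endpoint, so that imbalance feeds straight into the result. The article does not support this. The endpoint is change in body weight, and section 2.9 tests the group-by-time interaction, so a baseline offset in weight does not by itself enter the effect. BMI matters only as far as it predicts weight change, and the article gives no figure for that. If that correlation is 0.1 to 0.3 (assumption), perfect BMI balance would remove at most 0.1² to 0.3², that is 1% to 9%, of the variance of the effect estimate.

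A third reply is that candidates are found from medical records while the factor uses baseline BMI, so a few may have drifted to 25 or below. That is fair, and it is why the point says almost every participant rather than every one. It does not rescue the cut. Those few would fail Table 1 if it is applied again at baseline (unless exactly at 25), and everyone above 25 stays unsorted.

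Finally, it is tempting to say that the change is free because nobody has been randomised. Section 3 says "The intervention process has not yet been started", and section 4 says that participants could not yet attend for baseline measurement, which precedes randomisation. But section 3 also places the study in an initial intervention phase, and the abstract speaks of participants as already randomised. The timing is therefore not secure.

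**Conclusion.** The inconsistency between section 2.5 and Table 1 is real and does not depend on any assumption: the two BMI levels cannot divide an eligible population that starts at 25. The minimisation effectively runs on gender and HbA1c, and the statement that BMI will be balanced is not met by the rule given.

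The size is modest. About 16 percentage points in the share with BMI ≥30 is the edge of the 95% chance range under an assumed 50% share. It is neither an expected imbalance nor a bias in either primary endpoint. A reader might conclude that BMI is not balanced at all; the supportable statement is that it is not balanced by the minimisation. The loss is protection against chance imbalance, and some precision to the extent that BMI predicts weight change. That makes it a should-fix.

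**What to change.** First, the sponsor should confirm whether any participant has been allocated.

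- **If none has:** amend section 2.5 to a BMI cut inside the eligible range. The median BMI of the patients already identified, or 30 kg/m², would serve; these are examples of an allocation setting, and the entry criterion is untouched.
- **If allocation has begun:** apply the new cut to later allocations, or correct the statement that BMI is balanced.

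In either case, adjust the body-weight analysis for baseline BMI or baseline weight as a continuous covariate. A two-level BMI covariate would discard information. Height and weight are already collected at week 0 (Table 3), so no new data are needed.

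The cost is one setting in the minimisation program and a short amendment, which section 2.12 requires to go to the ethics committee. That is small but not nil. Once participants are allocated, any lost balance among them can only be adjusted for in the analysis.
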